#### *Other measures*

Participants will rate their thoughts about the treatment credibility and their treatment expectations after the first and last treatment sessions (Weeks 1 and 12) using a 4-item scale that has been previously described [72]. The first three questions are rated on a 11-point numerical rating scale from “0” (not at all confident) to “10” (absolutely confident) and pertain to the participants’ confidence in the treatment to manage and relieve their pain as well as their confidence in recommending the treatment to a friend in a similar condition. The last question assesses how logical the participant thought the treatment was and is rated on a 7-point numerical rating scale ranging from “0” (not logical at all) to “6” (very logical).

Participant adherence to the treatment program in all three groups will be obtained by recording the number of physiotherapy sessions attended (out of a maximum number of ten). Participants will maintain a daily logbook to record the number of home exercises and/or pain coping skills practice completed during the 12-week treatment phase. The physiotherapist will also indicate on an 11 point numeric rating scale, their perceived rating of the participant’s overall adherence to the treatment program with “0” (not at all) to "10" (completely as instructed) [73].

Home exercise adherence during the follow up period will be measured in the exercise only and the integrated exercise and PCST groups via a self-report questionnaire. This will be administered on four occasions (22, 32, 42 and 52 weeks). Participants will be asked how many times in the previous week they performed the home exercises. These will be summed over the four occasions (maximum of 12 exercise days). To assess the amount of home pain coping skills practice performed during the follow-up period, participants in the PCST alone group or the integrated group will be mailed a short questionnaire at weeks 22, 32, 42 and 52 which asks how many times they have performed each of the different skills practice in the previous week. Participants in all groups will provide a self-rating of their adherence to their specific home program using a similar 11 point numeric rating scale with “0” (not at all) to "10" (completely as instructed) at weeks 22, 32, 42 and 52. Furthermore, the usefulness of the various pain coping skills will be determined at weeks 32 and 52 in the PCST groups by a 5-point likert scale from “1” (not useful) to “5” (very useful).

Adverse events and the use of co-intervention will be recorded in the logbook during the treatment period and via questionnaire at weeks 12, 32, and 52 in the follow-up phase. Adverse events will be defined as any problem from the exercises and/or pain coping skills that lasted for more than two days and caused them to seek treatment.

Information on health care costs and direct non-health care costs over the entire study period (52 weeks) will be collected by questionnaire. Direct health care costs will include costs of physiotherapy attendance, additional health provider visits (doctors, specialists, other health care professionals), investigative procedures, purchase of prescription and over the counter medication, home care and hospitalization. Direct non-health care resources will include number of lost days from work.

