### Procedure

The procedure is outlined in Figure 1. Preliminary screening will be conducted over the telephone by a research assistant not involved in outcome assessment. Volunteers who are deemed potentially eligible will undergo a semiflexed posteroanterior x-ray of their painful knee (the more symptomatic knee in cases of bilateral eligible knee pain) at one of six trial radiology centres unless they can provide their own such films from within the previous 12 months. X-ray grading will be performed by two trained researchers at each site and any disagreement will be resolved through discussion or where necessary, by a third rater. A screening record will be maintained to document the criteria eliminating those found to be ineligible. Participants will attend the University of Melbourne or the University of Queensland for baseline testing, following which they will be randomised into one of three intervention groups: (i) exercise; (ii) PCST; or (iii) integrated exercise and PCST. Each intervention will last for 12 weeks and will involve 10 individual visits to a project physiotherapist together with home exercise and/or pain coping skills practice. Following the intervention, participants will continue their home exercise and/or pain coping skills practice unsupervised for nine months. Participants will be re-assessed at week 12 (immediately following the intervention), at week 32 (by postal questionnaires) and at week 52 (at the University). Additional questionnaires relating to home practice adherence will also be collected at weeks 22 and 42. Participants will also wear a pedometer for 7 consecutive days at baseline, 12 weeks and 52 weeks. All participants will be asked to refrain from seeking other forms of treatment during the trial. However, due to ethical considerations, analgesia and non-steroidal anti-inflammatory drugs will be permitted as required.

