### Follow-up period

During the 9-month unsupervised follow-up period, participants in the exercise only and integrated groups will be requested to continue their home strengthening program but this will be reduced to three times per week. Participants in the PCST and integrated groups will be requested to continue their PCST home practices as needed (Figure 1, Table 2). At weeks 22, 32, 42 and 52 participants will be requested to complete questionnaires posted to them pertaining to adherence to the home program. In addition, the treating physiotherapist will telephone participants at weeks 22, 38 and 46 to discuss progress with the aim of enhancing adherence to the home program. After the 9-month period (week 52), participants will attend a follow up testing session at the University laboratory.

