**Other measures**		
Treatment credibility	Treatment Credibility Scale	1, 12 weeks
Treatment session attendance	Therapist treatment records	During intervention
Home practice during treatment	Participant log book – number of days/times completed	Daily during intervention
	Therapist rating of participant adherence using 11-point numeric rating scale	12 weeks
	Self-rated using 11-point numeric rating scale	22, 32, 42, 52 weeks
Home practice during follow up	Questionnaire-number of days performed exercises/pain coping skills in past week	22, 32, 42, 52 weeks
	Questionnaire - usefulness of pain coping skills	32, 52 weeks
Adverse events	Participant logbook	Daily during intervention
	Questionnaire	32, 52 weeks
Healthcare usage and related costs	Questionnaire and health system	0, 12, 32, 52 weeks

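### After week 12, adverse events and co-interventions are asked about only at weeks 32 and 52, although every arm already returns posted questionnaires at weeks 22 and 42; the text and Table 4 also disagree on week 12

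*Protocol article*

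**What the plan says.** The Other measures section has adverse events and co-intervention use entered in a log book while treatment lasts, and collected "via questionnaire at weeks 12, 32, and 52 in the follow-up phase". An adverse event is defined there as "any problem from the exercises and/or pain coping skills that lasted for more than two days and caused them to seek treatment".

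Table 4 gives the adverse-event schedule in two lines: "Participant logbook Daily during intervention" and "Questionnaire 32, 52 weeks". It has no week 12 questionnaire for adverse events and no separate row for co-intervention.

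Treatment ends at week 12 (Procedure: "Each intervention will last for 12 weeks and will involve 10 individual visits to a project physiotherapist"). The unsupervised phase then runs to week 52 (Follow-up period: "After the 9-month period (week 52), participants will attend a follow up testing session at the University laboratory"). Within it, the Follow-up period section says: "At weeks 22, 32, 42 and 52 participants will be requested to complete questionnaires posted to them pertaining to adherence to the home program". Other measures confirms that all three groups rate their adherence at those four time points. The treating physiotherapist also telephones at weeks 22, 38 and 46, to talk about progress and support adherence. No adverse-event recording is described for the week 22 and 42 mailings or for the calls.

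**The concern.** Adverse-event capture changes at week 12 from a daily log to a questionnaire every 20 weeks. This happens when clinic visits stop and home strengthening continues unsupervised. Events and co-interventions that are asked about 20 weeks later may be forgotten or misdated. A participant lost between weeks 12 and 32 contributes no follow-up adverse-event data under the printed schedule. The sample size section allows for 10% dropout but does not say when it is expected to occur.

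What is at stake is the description of safety and of co-intervention over the 40 weeks. H5 expects exercise adherence in this phase to be higher in the integrated arm than with exercise alone. If so, exposure may differ between those arms in the period when events are recorded least often.

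Separately, the text and Table 4 give different schedules at week 12, and both cannot be followed.

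**Working it through.** **Inputs from the protocol article**

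- Treatment phase: weeks 0 to 12 (Procedure).
- Unsupervised phase: week 12 to week 52, so 52 − 12 = 40 weeks (Follow-up period).
- Prescribed home exercise: four sessions a week in treatment (Exercise intervention) and three a week in follow-up (Follow-up period, Table 2).
- Adverse-event questionnaires: weeks 12, 32 and 52 (Other measures text); weeks 32 and 52 (Table 4).
- Posted questionnaires that already exist: weeks 22, 32, 42 and 52 (Follow-up period).
- Telephone calls: weeks 22, 38 and 46 (Follow-up period).
- Healthcare-use questionnaire: weeks 0, 12, 32 and 52 (Table 4).

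**The plan's own figure.** The article gives no adverse-event figure. The one figure built on the follow-up prescription is the maximum of 12 exercise days summed over four one-week questionnaires (Other measures). 4 × 3 = 12, so it reproduces.

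**Share of prescribed exercise in the unsupervised phase (exercise and integrated arms only)**

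- Treatment: 12 × 4 = 48 sessions.
- Follow-up: 40 × 3 = 120 sessions.
- Share: 120 / (48 + 120) = 120/168 = 71.4%.
- With nine months taken as 39 weeks: 117/165 = 70.9%.
- With home exercise assumed to fill only 11 or 10 of the 12 treatment weeks: 120/164 = 73.2% or 120/160 = 75.0%.

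**Interval between adverse-event queries after treatment**

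| Schedule | Queries after week 12 | Intervals (weeks) | Longest |
|---|---|---|---|
| As printed | 32, 52 | 20, 20 | 20 |
| With the existing mailings | 22, 32, 42, 52 | 10, 10, 10, 10 | 10 |

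The article does not print the questionnaire's recall window. Twenty weeks is the gap between queries, and so the look-back needed for full coverage. A shorter window would leave part of the phase uncovered.

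**Contacts of any kind after week 12.** Mailings and calls together fall at weeks 22, 32, 38, 42, 46 and 52. The gaps are 10, 10, 6, 4, 4 and 6 weeks, so the longest period without any contact is 10 weeks.

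**Week 12, text against table.** The text includes a week 12 questionnaire and Table 4 does not. The text also places week 12 in the follow-up phase, although it is the end of treatment. Both sources have the log book running through treatment.

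**The case against.** The case for leaving the schedule alone has real substance.

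- **The definition is demanding.** A problem must last more than two days and also lead the participant to seek treatment. Brief, untreated complaints, which are the easiest to forget, are not adverse events here. This stands, and it weakens the recall argument.
- **Participants are not out of contact.** A reader might infer that nobody could learn of a problem for up to 20 weeks. The document does not support that: the calls and mailings leave at most 10 weeks without contact. But no adverse-event recording is assigned to the calls or to the week 22 and 42 mailings, so these contacts do not make up for the missing query.
- **There is a second source.** Because an event must involve treatment seeking, the healthcare-use questionnaire overlaps with it and covers the full 52 weeks. It gives a partial cross-check, but after treatment it is completed at the same weeks 32 and 52 and, as described, does not attribute cause.
- **The log book is checked.** Table 2 has the physiotherapist look at it in sessions 2 to 10, so a participant who stops keeping it would probably be noticed. A reader might infer that the week 12 mismatch leaves treatment-phase counts unreliable, or unequal between arms. Nothing in the document shows that.
- **The 71% is an exposure figure.** It counts prescribed sessions, not performed ones, and the Background section itself says that exercise adherence declines. It does not apply to the arm that receives pain coping skills training alone, and it says nothing about how many events are missed.
- **The arms are treated alike.** All three have the same schedule, and no comparison of supervised with unsupervised safety is planned. A reader might infer that a stated comparison is biased; the document does not support that.
- **The article condenses a fuller protocol.** Questionnaire wording may well sit there. The collection weeks, however, are printed here, and they conflict with each other.

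Asking at two points is a defensible choice for a home programme, not an error. What remains is a cheap improvement that the existing mailings make possible, and one inconsistency.

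**Conclusion.** The concern holds in a limited form. After week 12 the plan asks about adverse events and co-interventions only twice, 20 weeks apart, while two further mailings to every arm go unused for this purpose. About 71% of prescribed home sessions in the two exercising arms fall in this phase (71% to 75% under the alternatives shown). Under-reporting is plausible. Its size cannot be derived from the document and is probably modest, given the treatment-seeking criterion, the telephone calls and the healthcare-use questionnaire.

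The effect is confined to the description of safety and co-intervention after treatment. The primary comparison at 12 weeks is untouched.

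The week 12 disagreement between the Other measures text and Table 4 is the only outright contradiction. It is minor because the daily log book covers weeks 0 to 12 in both versions. The conclusion assumes that the printed weeks are the complete adverse-event schedule and that each questionnaire is meant to cover the time since the one before.

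**What to change.** 1. Add the same adverse-event and co-intervention items to the questionnaires already posted at weeks 22 and 42, in all three arms. At every post-treatment query, ask about the time since the previous one. The longest interval falls from 20 to 10 weeks, and the number of post-treatment queries rises from two to four.
2. Amend the Other measures text and the Table 4 adverse-event row together so that they state one schedule. Changing the table alone to include weeks 22 and 42 would create a new mismatch with the text.
3. In the same edit, reconcile the week 12 questionnaire, which the text has and the table lacks, and describe week 12 as the end of treatment. If it is kept, say that it covers the whole treatment phase whether or not the log book is returned.

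The cost is a few more items on two existing mailings, with slightly more participant burden and data entry, plus an edit to one sentence and one table row. No extra visits or staff are needed.

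### An adverse event must be attributed to the programme, last over two days and lead to treatment-seeking, all at once, so harms are under-counted and comparability between arms is not assured

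*Protocol article*

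**What the plan says.** The only adverse event definition in the protocol article is in Other measures: "any problem from the exercises and/or pain coping skills that lasted for more than two days and caused them to seek treatment". The same paragraph says that adverse events and co-interventions are "recorded in the logbook during the treatment period and via questionnaire at weeks 12, 32, and 52 in the follow-up phase". Table 4 lists the participant logbook daily during the intervention, and the adverse event questionnaire at weeks 32 and 52 only.

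Under Procedure, the article states that "All participants will be asked to refrain from seeking other forms of treatment during the trial", and then that "analgesia and non-steroidal anti-inflammatory drugs will be permitted as required". It does not define what counts as seeking treatment for the adverse event definition.

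**The concern.** The conditions are joined by a conjunction, so failing any one of them removes the problem from the count. Duration and treatment-seeking are each reasonable markers of a consequential event. Required together, they exclude events that either would have caught alone.

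Two of the conditions also depend on the participant's judgement or behaviour, and these may vary by arm. Participants know which programme they received, so the same knee flare may be put down to the exercises in an exercise arm and to the disease itself in the PCST arm. PCST aims to raise self-efficacy and reduce catastrophising, and its last session develops coping plans (Table 3). Participants in the PCST and integrated arms may therefore be more or less inclined to seek care for the same problem.

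What is at stake is any later statement that a programme was free, or nearly free, of adverse events, and any comparison of harms between arms. The efficacy analyses are not affected.

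**Working it through.** The article gives no adverse event rate, so there is no figure to reproduce. The check applies the definition to typical cases. The cases are invented for illustration.

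| Case | Attributed to programme | Over two days | Treatment sought | Counted as written |
|---|---|---|---|---|
| A. Three-week flare, tolerated or met by stopping the exercises | yes | yes | no | no |
| B. Acute problem needing medical care, settled within two days | yes | no | yes | no |
| C. Three-week flare taken to a doctor, thought to be the disease | no | yes | yes | no |
| D. Three-week flare managed only with permitted analgesics | yes | yes | undefined | unclear |
| E. Three-week flare taken to a doctor, thought due to the exercises | yes | yes | yes | yes |
| F. One day of soreness, nothing done | yes | no | no | no |

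Leaving out F is a sensible threshold. Leaving out A and B follows directly from the conjunction and needs nothing from the Procedure section. C turns on perceived cause. D cannot be settled from the text.

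**Size of the under-count (assumed values only).** Among problems attributed to the programme, the share counted is

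P(over two days) × P(treatment sought, given over two days).

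Take assumed ranges of 0.3 to 0.7 for the first factor and 0.2 to 0.6 for the second:

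- low end: 0.3 × 0.2 = 0.06
- high end: 0.7 × 0.6 = 0.42

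The share counted would lie between 6% and 42%. Not everything lost is an important harm, because case F is in the denominator too. A rule of over two days or treatment would keep at least the first factor, 30% to 70%, on the same assumptions. These figures show how the rule behaves. They do not estimate this trial.

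**Between arms.** Let p1 and p2 be the true rates in two arms and c1 and c2 the shares counted.

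- Recorded difference: c1·p1 − c2·p2.
- Recorded ratio: (c1/c2) × (p1/p2).

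If c1 = c2 = c, the difference shrinks to c(p1 − p2) and the ratio is unchanged. If only treatment-seeking differs, within the assumed 0.2 to 0.6, then c1/c2 can lie anywhere from 0.2/0.6 = 0.33 to 0.6/0.2 = 3. The recorded ratio can then move either way, and nothing in the article fixes which.

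**Questionnaire times.** The text has "via questionnaire at weeks 12, 32, and 52 in the follow-up phase", while Table 4 has weeks 32 and 52. The daily logbook covers the intervention in both places, so the mismatch leaves no period uncovered. It is still an inconsistency about one instrument.

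**The case against.** A threshold that separates consequential problems from ordinary exercise soreness is defensible, and this one is stated openly. Participants enter with pain of at least 40 on a 100 mm scale, so recording every worsening would also pick up normal fluctuation of the disease. None of the hypotheses H1 to H7 concerns harm, the Statistical analysis section names no adverse event comparison, and Table 4 places adverse events under other measures. Co-interventions, provider visits, medication and hospitalization are collected as well, and the global change scales run down to much worse, so sustained worsening and medical contact are partly visible elsewhere.

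Much of this stands as a limit on importance. It does not rescue the definition. Health-care use is collected for costing, none of these data are tied to the adverse event definition, and the care records miss harms for which no care was sought. The threshold can also be kept as a reported subset, so broader recording loses nothing.

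A reader might infer three stronger points, which the document does not support:

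- **That the trial forbids the very behaviour on which its definition depends.** The request concerns other forms of treatment, analgesia and NSAIDs are permitted, and the article does not say whether taking these, or raising a problem with the project physiotherapist, counts as seeking treatment. The clash is partial.
- **That a flare managed with permitted analgesics is certainly excluded.** That is one reading of an undefined term.
- **That the harm comparison is biased towards no difference.** Equal loss in each arm leaves the ratio intact, and unequal loss can push either way.

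**Conclusion.** The concern holds in limited form. As written, the definition under-counts harms: it excludes prolonged problems for which no treatment was sought and short problems that needed care. Comparability between arms is not assured, because attribution and treatment-seeking may differ between participants who know their programme and are trained differently in coping. The direction and size of any between-arm bias cannot be determined from the article. The 6% to 42% range rests wholly on assumed probabilities.

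The request to refrain from other treatment may add to the under-count, but the conclusion does not depend on it. Nor does it depend on anything a fuller protocol might add about serious events, since the point concerns the definition that the article does state. No efficacy conclusion is affected. This is a cheap improvement: without it, a report of few or no adverse events would be weakly supported.

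**What to change.** Change the measurement only, within the existing logbook and questionnaires:

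1. In all three arms, record any new or worsened problem that lasted more than two days **or** led to treatment, whatever its perceived cause.
2. Record duration, relatedness and treatment-seeking as descriptors of each event, not as entry conditions.
3. State what counts as seeking treatment, including the status of permitted analgesia and NSAIDs and of raising the problem with the project physiotherapist, so that Other measures and Procedure can be read together. This implies no view on what treatment participants should be allowed.
4. Report events by arm, with the present definition kept as a subset. Every event that it counts now is still counted.
5. Reconcile the adverse event questionnaire times in the text (weeks 12, 32 and 52) with Table 4 (weeks 32 and 52).

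The cost is new wording in two instruments and more minor events to tabulate, including ordinary disease fluctuation. The article gives no basis for estimating how many more.
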